# Effectiveness of a Blended Multidisciplinary Intervention for Patients with Moderate Medically Unexplained Physical Symptoms (PARASOL): Protocol for a Cluster Randomized Clinical Trial

**DOI:** 10.2196/resprot.9404

**Published:** 2018-05-08

**Keywords:** medically unexplained physical symptoms, blended care, multidisciplinary, primary care, intervention

## Abstract

**Background:**

Medically unexplained physical symptoms are an important health problem in primary care, with a spectrum from mild to chronic. The burden of chronic medically unexplained physical symptoms is substantial for patients, health care professionals, and society. Therefore, early identification of patients with moderate medically unexplained physical symptoms is needed in order to prevent chronicity. The preventive screening of medically unexplained physical symptoms (PRESUME) screening method was developed using data from the electronic medical record of the patients' general practitioner and demonstrated its prognostic accuracy to identify patients with moderate medically unexplained physical symptoms. In the next step, we developed a proactive blended and integrated mental health and physical therapy intervention program (PARASOL) to reduce complaints of moderate medically unexplained physical symptoms, stimulate self-management, and prevent chronicity.

**Objective:**

The primary objective of this study is to investigate the effectiveness of the blended PARASOL intervention on the impact of symptoms and quality of life in patients with moderate medically unexplained physical symptoms compared with usual care. Secondary objectives are to study the effect on severity of physical and psychosocial symptoms, general health, physical behavior, illness perception, and self-efficacy in patients with moderate medically unexplained physical symptoms as well as to determine the cost-effectiveness of the program.

**Methods:**

This paper presents the study protocol of a multicenter cluster randomized clinical trial. Adult patients with moderate medically unexplained physical symptoms will be identified from electronic medical record data using the PRESUME screening method and proactively recruited for participation in the study. Cluster randomization will be performed at the level of the participating health care centers. In total 248 patients with moderate medically unexplained physical symptoms (124 patients per arm) are needed. The PARASOL intervention is a 12-week blended primary care program consisting of 4 face-to-face consultations with the mental health nurse and 5 physical therapy sessions, supplemented with a Web-based program. The Web-based program contains (1) information modules and videos on self-management and educative themes, (2) videos and instructions on prescribed home exercises, and (3) assignments to gradually increase the physical activity. The program is directed at patients’ perception of symptoms as well as modifiable prognostic risk factors for chronicity using therapeutic neuroscience education. It encourages self-management, as well as an active lifestyle using a cognitive behavioral approach and graded activity. Primary outcomes are impact of symptoms and quality of life. Secondary outcomes are severity of physical and psychosocial symptoms, general health, physical behavior, illness perceptions, self-efficacy, and cost-effectiveness. All measurements will be performed at baseline, 3 and 12 months after baseline. Retrospective cost questionnaires will also be sent at 6 and 9 months after baseline and these will be used for the cost-effectiveness analysis.

**Results:**

The intervention has been developed, and the physical therapists and mental health nurses in the participating experimental health care centers have received two days of training on the content of the blended PARASOL intervention. The recruitment of health care centers started in June 2016 and inclusion of patients began in March 2017. Follow-up assessments of patients are expected to be completed in March 2019.

**Conclusions:**

This study is the first randomized clinical trial to determine the effectiveness (including cost-effectiveness) of a proactive, blended, and integrated mental health and physical therapy care program for patients with moderate medically unexplained physical symptoms. The findings will help to improve the treatment for patients with moderate medically unexplained physical symptoms and prevent chronicity.

**Trial Registration:**

Netherlands Trial Register NTR6755; http://www.trialregister.nl/trialreg/admin/rctview.asp?TC=6755 (Archived by WebCite at http://www.webcitation.org/6ywporY7u).

## Introduction

Medically unexplained physical symptoms (MUPS), especially pain, dizziness, and fatigue are frequent in primary care, in fact 25%-50% of all symptoms presented during consultations cannot be adequately medically explained [1]. If there are physical complaints for which no medical condition can be found after adequate medical examination, they will be defined as MUPS [2,3].

MUPS can be regarded as a spectrum ranging from mild unexplained physical symptoms (low incidence, one or two domains, low impact), to moderate symptoms (more frequent, two or three domains, higher impact) and finally to persisting or chronic MUPS (high impact, more clusters involved, chronic; eg, fibromyalgia, chronic fatigue syndrome, or irritable bowel syndrome) [3,4]. In this spectrum, mild MUPS have an estimated prevalence of 70% to 80% [4,5]. These patients consult their general practitioner (GP) for a symptom that cannot be explained immediately, but the symptoms improve within 2 weeks [6]. Moderate MUPS have an estimated prevalence of approximately 15%, where patients still experience unexplained symptoms after three months without a diagnosis of a functional somatic syndrome [6]. Patients with chronic MUPS will have a symptom duration of at least six months, with the presence of a functional somatic syndrome, such as fibromyalgia, chronic fatigue syndrome or irritable bowel syndrome, or a somatic symptom disorder according to the Diagnostic and Statistical Manual of Mental Disorders, 5th edition [4,6,7]. Patients with chronic MUPS occur in approximately 2.5% in primary care, and 3% of the GP consultations are MUPS consultations [1,8].

Despite the low prevalence of chronic MUPS, the burden is substantial [1], with a high impact on patients’ quality of life and daily functioning. Compared with the general population, as well with other patient groups such as major depressive disorder and cancer patients, patients with chronic MUPS report a lower quality of life [9,10]. Moreover, patients with MUPS consult a GP more frequently, but GPs find adequate management of MUPS challenging [11].

GPs frequently focus on exclusion of a somatic disease by recommending somatic interventions such as drug prescriptions, an investigation or a referral to a specialist; while patients often do not request for somatic interventions [12]. Furthermore, GPs face difficulty in the timely recognition of patients with MUPS [13]. On average, it takes two years to obtain a diagnosis. During this time period patients have on average 15 GP consultations, 8 visits to a hospital specialist and 14 sessions with the physical therapist [10]. Almost 40% of patients with MUPS report absenteeism from work [10]. As a result, MUPS are associated with increased direct and indirect costs related to health care expenditure as well as work and insurance related costs [10,14].

Much research has been conducted on effective interventions for chronic MUPS. Neurosciences-based therapeutic education, cognitive behavioral therapy, and exercise therapy have been shown to be effective treatment modalities in patients with MUPS [15-18]. Overall, the vast majority of these studies included patients with chronic MUPS. So far little research has been conducted in patients with moderate MUPS, partly due to the fact that adequate methods for early identification are lacking. Early identification of patients with moderate MUPS would enable interventions directed at prevention of chronicity, which ultimately might decrease the burden of these symptoms for patients, health care professionals and society.

Recently, a screening method (PRESUME; preventive screening of medically unexplained physical symptoms) has been developed to identify patients with moderate MUPS using data from the electronic medical record of the patient’s GP as shown in Figure 1 [19]. The PRESUME screening method showed acceptable prognostic accuracy over a five-year follow-up [19]. For patients with moderate MUPS, we developed a proactive, blended, and integrated mental health and physical therapy care program to prevent chronicity. This is a 12-week program consisting of 4 face-to-face consultations with the mental health nurse and 5 physical therapy sessions, which are supplemented with a Web-based program (e-Exercise). Blended care has already proven to be effective in other studies [20,21] and it helps to promote self-management.

**Figure 1 figure1:**
[figure not shown]
PRESUME screening method.

The primary objective of the present study is to investigate the effectiveness of the proactive, blended and integrated mental health and physical therapy care program (PARASOL) on impact of symptoms, as well as the physical and mental dimensions of quality of life in patients with moderate MUPS in comparison with usual care. Secondary objectives are to study the effect on severity of (psychosocial) symptoms, general health, physical behavior, illness perception, and self-efficacy in patients with moderate MUPS as well as to determine the cost-effectiveness of this program.

## Methods

### Study Design

A prospective, multicenter cluster randomized clinical trial will be conducted. The study has been approved by the Medical Ethical Committee of University Medical Center Utrecht, the Netherlands. The blended PARASOL intervention will be compared with usual care. An overview of the study procedure is shown in Figure 2.

### Participants

#### Patient selection

Patients with moderate MUPS will be identified in the participating practices using 3 strategies. The first strategy is to use the PRESUME screening method. All patients in the routine care database of a GP are anonymously screened in a stepwise selection, based on a consultation frequency above five, with exclusion of chronic diseases (eg, chronic obstructive pulmonary disease, hypertension or diabetes mellitus) and psychiatric diagnoses (eg, schizophrenia, anxiety disorder or depressive disorder) and the presence of any of the 104 MUPS related International Classification of Primary Care codes. The prognostic accuracy of this PRESUME screening method for identification of moderate MUPS patients is moderate [19].

**Figure 2 figure2:**
[figure not shown]
Overview of the study.

Since the PRESUME screening method is over inclusive and not meant to set an accurate diagnosis of MUPS in individual patients, all identified patients with moderate MUPS will be screened by their GP for eligibility [19]. As a consequence, the expected prevalence of patients with moderate MUPS is less than the 2.4% according to the PRESUME screening method [19]. The GP will exclude patients based on the following criteria: (1) having another chronic somatic or psychiatric disease, (2) receiving a medically explained diagnosis between identification using the PRESUME screening method and the time of inclusion, (3) having complaints with a duration of less than 1 month, in which case further diagnostic evaluation of the symptoms is needed, and (4) unable to participate as determined by the GP, due to a life-threatening condition, a shortened life expectancy, a major life event in the past month or a MUPS targeted multidisciplinary intervention in the past 12 months.

All remaining eligible patients will proactively be approached by their GP, by sending them an invitation letter with study information.

Secondly, GPs will recruit patients during consultations if they meet the following criteria: ≥18 years of age, ≥5 general practice consultations during the past twelve months, medically unexplained physical symptoms, and the diagnostic phase is completed. When a patient is eligible, the GP can give the contact details of the researchers of the PARASOL study to the patient.

The last strategy will be open recruitment in participating health care centers. Flyers with information about the PARASOL study will be provided in the waiting rooms and included in the newsletter of the health care centers. Patients who are willing to participate can contact the researcher by phone or by mail. Subsequently, the researcher will determine whether the patient is eligible by asking if the patient is older than 18 years, has had ≥5 general practice consultations during the past twelve months, and if the patient has medically unexplained physical symptoms.

All patients who are willing to participate in the PARASOL study, will have to have access to the internet and have mastered the Dutch language. When a patient is willing to participate, they can contact the researcher by phone or email. The researcher will answer any possible questions, give further information, and will make an appointment for the patient to sign informed consent and a baseline measurement evaluation. Additionally, patients in the intervention group will be invited to participate in the blended PARASOL intervention.

#### Study centers

The Leidsche Rijn Julius Health Care Centers (LRJG; 5 health care centers with 40,000 patients) and the Eindhoven Corporation of Primary Health Care Centers (SGE; 10 health care centers, 70,000 patients) will participate in the study. All relevant disciplines—general practitioners, physical therapists, and mental health nurses—are available and willing to participate.

### Randomization Procedure

Cluster randomization will be performed at the level of the participating health care centers. Health care centers will randomly be assigned to either the intervention group or the control group (usual care) using a Web-based random generation of a sequence of numbers. Through cluster randomization, we will avoid professionals within one health care center offering both the blended PARASOL intervention and usual care, as this could cause potential contamination effects [22]. A higher drop-out rate in the intervention group is expected since psychological therapies have a 7% higher proportion of drop outs compared with usual care [18]. The blended PARASOL intervention combines both mental health and physical therapy sessions. Therefore, an unequal randomization on cluster level will be conducted. Of the 15 included health care centers, 8 will be randomized to the blended PARASOL intervention and 7 will be randomized to the control group. After randomization of the health care centers, the selection and inclusion procedure of patients with moderate MUPS will be performed.

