The first identified limitation of this study, is that it is unblinded. Patients, health care professionals, and the researchers are aware all of the group allocated to the blended PARASOL intervention. This may lead to bias mechanisms such as response bias or observer bias being present in the data [53]. One of the aims of the training provided to the healthcare professionals involved in the study is to avoid response bias from the health care professionals. Observer bias will be avoided by using a measurement protocol, well trained observers, and standardized outcome measures. A second limitation is that overtreatment may occur since not all patients with moderate MUPS will be prevented from developing chronic MUPS after completing the PARASOL intervention. This could lead to higher health care costs if patients are still consulting health care professionals after completing the PARASOL intervention. However, an early intervention for patients with moderate MUPS may lead to a decrease of direct and indirect costs on long term if chronic MUPS is prevented. Therefore, one of the secondary objectives is to determine the cost-effectiveness of the PARASOL intervention. A third limitation is complexity of the design of the study due to the use of cluster randomization. Cluster randomized trials are more complex, require more patients to obtain equivalent statistical power, and require more complex analysis [43]. However, in the sample size calculation and statistical analysis, this possible design effect has been taken into account.

This study is the first trial that investigates the effectiveness (including cost-effectiveness) of a blended care program in patients with moderate MUPS. Therefore, this study will provide relevant results regarding short- and long-term effectiveness of a multidisciplinary, blended care program to prevent chronic MUPS.

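### Patients are selected after centres are randomised, by GPs and researchers who know the arm and partly through opportunistic routes, so patient selection can differ between arms

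*Protocol article*

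**What the plan says.** **Order.** Under Randomization Procedure, 15 centres are allocated 8 to 7, and then: "After randomization of the health care centers, the selection and inclusion procedure of patients with moderate MUPS will be performed".

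**Who knows the arm.** The limitations part of the Discussion says: "Patients, health care professionals, and the researchers are aware all of the group allocated to the blended PARASOL intervention".

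**How patients enter** (Methods, Patient selection):
- Route 1 begins with a rule-based search of the records: "All patients in the routine care database of a GP are anonymously screened in a stepwise selection". The GP then acts as gatekeeper, since "all identified patients with moderate MUPS will be screened by their GP for eligibility". One ground for exclusion is that the patient is "unable to participate as determined by the GP", with specified reasons. The remaining patients receive an invitation letter.
- Route 2 is opportunistic: "Secondly, GPs will recruit patients during consultations if they meet the following criteria". The criteria are short and do not repeat the route 1 exclusion list.
- Route 3 is self-referral after flyers and a newsletter: "The last strategy will be open recruitment in participating health care centers". The researcher settles eligibility by asking about age, number of consultations and unexplained symptoms. No GP check is stated.

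**Mitigation.** The Statistical Analysis section plans descriptive counts by route, baseline comparability checks, and a longitudinal mixed analysis adjusted for confounders that are given as examples. The Discussion offers controls the programme after the study. It gives response bias and observer bias as examples of what lack of blinding may cause.

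**The concern.** In a cluster trial, randomising centres balances centres in expectation. It balances patients only if they are identified and enrolled without regard to the arm. Here every step after the record search comes after allocation and involves someone who may know it: the GP who excludes, the GP who recruits in a consultation, the researcher who accepts a self-referral, and possibly the patient who decides whether to join.

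The article itself supplies reasons why this could matter. Its Discussion expects that controls may be less motivated to take part because they do not receive the programme, although it applies this only to drop-out. It also expects the proactive route to reach some people who currently have no symptoms or no wish for treatment. People who come forward in a consultation or after a flyer may differ from them. If the mix of routes, or the GP's threshold for exclusion, differs by arm, the arms contain different kinds of patients. An observed difference could then not be cleanly attributed to the intervention. Both primary outcomes are self-reported and plausibly depend on current symptoms.

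**Working it through.** **1. The passages side by side**

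| Step | Before or after allocation | Who decides | Protected from knowledge of arm? |
|---|---|---|---|
| Record search (route 1) | After | Fixed rules, anonymous | Largely yes |
| GP exclusion (route 1) | After | GP, partly by judgement | No |
| Recruitment in consultation (route 2) | After | GP | No |
| Self-referral (route 3) | After | Patient, then researcher | Researcher no; patient not stated |
| Consent | After | Patient | Not stated |

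Entry rules also differ by route. The record search requires a consultation frequency above five; routes 2 and 3 require five or more. The GP exclusion list is attached to route 1 alone. A different mix of routes therefore means a different population.

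**2. What a difference in mix could do**

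The article gives no figure for this bias, so there is none to reproduce. The route shares and patient differences below are assumptions.

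Imbalance b = (share of opportunistic patients in one arm − share in the other) × mean difference d between opportunistic and listed patients.
- Shares 50% and 20%: 0.30 × 5 = 1.5 points; 0.30 × 10 = 3.0 points, or 15% to 30% of the 10-point target.
- Milder case: (0.30 − 0.10) × 5 = 1.0 point.
- More extreme case: (0.50 − 0.10) × 15 = 6.0 points.

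**3. Effect on the type I error if b is left unadjusted**

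Inputs from the Sample Size section: SD 23.8, intracluster correlation 0.04, 20 patients per centre, 206 patients analysed (103 per arm). A two-sided test at 0.05 is assumed. The 206 is taken as given. The usual formula on the same inputs gives 89 × 1.76 ≈ 157 per arm, or 314, but that is a separate matter and this point does not depend on it.

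- Design effect at 20 per centre: 1 + 19 × 0.04 = 1.76. SE = 23.8 × √(2 × 1.76/103) = 4.40.
- Design effect with 206 patients over 15 centres (13.7 each): 1 + 12.73 × 0.04 = 1.51. SE = 23.8 × √(2 × 1.51/103) = 4.07.
- Type I error = Φ(b/SE − 1.96) + Φ(−b/SE − 1.96).

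| b (points) | b in SD | SE 4.40 | SE 4.07 |
|---|---|---|---|
| 0 | 0 | 0.050 | 0.050 |
| 1 | 0.04 | 0.056 | 0.057 |
| 2 | 0.08 | 0.074 | 0.078 |
| 3 | 0.13 | 0.105 | 0.114 |
| 4 | 0.17 | 0.149 | 0.166 |
| 5 | 0.21 | 0.206 | 0.233 |

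The error is larger with the smaller SE, so more patients would not cure it.

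**4. What baseline measurement changes**

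RAND-36 is measured at baseline. If selection shifts baseline and follow-up by the same b, a comparison of change has no bias from it. A baseline-adjusted comparison keeps b × (1 − β), where β is the within-arm slope of follow-up on baseline. For a stable difference in level, the table is therefore an upper limit. It does not bound bias from different trajectories, such as patients enrolled in a bad spell who then improve. Baseline adjustment may help the adequate-relief outcome less, because response is counted over repeated follow-up reports.

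**The case against.** The sequence is disclosed openly and contradicts nothing else in the article. Four counter-arguments deserve weight.

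- **Stronger readings.** A reader might infer that randomisation gives no protection, that motivated patients will enter preferentially in intervention centres, or that patients know their arm before consenting. The documents support none of these. Centre-level characteristics remain randomised. No passage shows preferential entry, and the later offer of the programme to controls works against it. The Patient selection section mentions consent and baseline before it mentions inviting intervention patients to the programme. It does not say that the letter or flyer reveals the arm. The Discussion says that patients are aware of the allocation, not when they learn it.
- **Safeguards.** The anonymous search, the baseline checks and an open-ended confounder list all reduce the risk. This stands, but two routes bypass the search, GP and patient decisions follow it, and adjustment reaches only measured factors.
- **Matters left to an analysis plan.** Whether route is modelled, or a sensitivity analysis is run, may be settled in a plan that is not shown. Its absence here is not the point; the order of steps that the article fixes is.
- **Timing.** Inclusion began in March 2017 and follow-up was due to end in March 2019. With 12 months of follow-up, that implies last inclusion around March 2018, and the article appeared in May 2018. Re-ordering steps may therefore have little or no scope left. This stands and limits the first part of the fix.

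The illustration is also open to challenge, since its route shares and patient differences are assumed and it ignores baseline adjustment. It shows how the mechanism scales and is not an estimate.

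**Conclusion.** The concern holds as a risk at patient level. Patients are identified, screened and recruited after allocation by people who know it, and two of three routes bypass both the anonymous search and the exclusion list stated for the first. The arms can therefore differ by selection in a way that a mixed analysis with adjustment for measured confounders may not remove.

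The size and direction are unknown. Under the assumed shares and differences above, the imbalance runs from about 1 to 6 points. An unadjusted 3-point difference would roughly double the nominal type I error, to 0.105-0.114. Adjustment for baseline would shrink the part that is a stable difference in level. It would be wrong to conclude that the comparison is unprotected or that bias has been shown. The article's list of biases from lack of blinding is illustrative, but leaving this one unnamed is a gap worth closing. The remedies are cheap and would change how far a difference between arms can be attributed to the programme.

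**What to change.** 1. **Recruitment.** For any centre or patient not yet recruited, complete the PRESUME extraction and the GP exclusion before allocation is disclosed. Use one invitation that does not reveal the arm, and obtain consent and baseline before the patient is told it. For centres already open, re-run the rule-based query on records dated to randomisation and freeze that list.
2. **Analysis and reporting.** Prespecify a sensitivity analysis restricted to recruited patients on the frozen list, defined by list membership and not by route of entry. Adjust all analyses for the baseline value of the outcome where it is measured. Report identified, excluded, invited and consented counts where they can be known, with baseline characteristics, by arm and route. Keep route out of the primary model: it is determined after randomisation and may itself be affected by the arm, so conditioning on it can introduce bias. Use it only in sensitivity analysis.
3. **Limitations.** Name identification and recruitment bias.

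**Cost.** One dated query per open centre, fuller flow reporting and one extra analysis. The list-restricted analysis has fewer patients and is less precise. In centres already open, it does not remove differential GP exclusion or differential consent, so agreement with the main result would be reassuring but not conclusive.
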